### Study population

We aim to enroll 60 participants (30 per group), aged 50 to 90, with a confirmed diagnosis of ischemic or hemorrhagic stroke occurring at least six months prior to enrollment. The sample size was informed by previous feasibility studies of complementary health interventions (Richard-Lalonde et al., 2023; Doorley et al., 2022; Portz et al., 2023; Smith et al., 2022). Participants will be excluded if they meet any of the following criteria: (1) significant hearing loss, defined by a score >26 on the Hearing Handicap Inventory for the Elderly Screening (HHIE-S; Ventry and Weinstein, 1982); (2) contraindications for MRI; (3) cognitive impairment that may interfere with completion of study procedures, defined as a Montreal Cognitive Assessment (MoCA; Nasreddine et al., 2005) score below 22 (unless the lower score is attributable to expressive aphasia); (4) specific musical anhedonia, defined as a score below 60 on the Barcelona Music Reward Questionnaire (BMRQ; Mas-Herrero et al., 2013); or (5) amusia, defined as a score below 70% on the Montreal Battery of Evaluation of Amusia (MBEA; Peretz et al., 2003). Participants will not be excluded if they are currently taking medications that may affect brain function (e.g., antidepressants) or if they are engaged in other complementary therapies (e.g., mindfulness, yoga). However, they will be instructed not to initiate any new medications or therapies during the study period. Participants who begin a new treatment during the study will be excluded from the analysis. Participants will also be discontinued from the study upon their request or if there is a worsening of their medical condition that compromises safety or study participation.

Eligible patients will be contacted by phone, and the study will be explained using a standardized script. Patients who do not make an immediate decision (e.g., need time to consider participation) will receive up to two follow-up contacts via phone or email over a two-week period. To meet recruitment targets, we aim to enroll at least five participants per month over the course of 12 months.

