### Procedures and assessments

#### Screening

Eligibility will be assessed using a well-characterized stroke registry. Initial screening will verify age and confirm a diagnosis of ischemic or hemorrhagic stroke occurring at least six months prior to enrollment. Additional exclusion criteria will then be reviewed. If data for key screening measures are missing from the registry, a study team member will contact the patient to explain the study and gauge interest. If the patient agrees to participate, they will complete a screening session (online or in person) to confirm eligibility. This session may include: (1) the Hearing Handicap Inventory for the Elderly – Screening version (HHIE-S; Ventry & Weinstein, 1982), a 10-item self-report measure of hearing loss validated against pure-tone audiometry (Lichtenstein et al., 1988); (2) the Montreal Cognitive Assessment (MoCA), a standardized screening tool used to detect cognitive impairment and early signs of dementia (Nasreddine et al., 2005). The MoCA assesses multiple cognitive domains, including executive function (e.g., trail-making), visuospatial abilities (e.g., clock-drawing), attention (e.g., digit span), language (e.g., sentence repetition and verbal fluency), abstraction (e.g., identifying similarities between two concepts), short-term memory (via a delayed recall task), and orientation (e.g., stating the current date, month, and year); (3) the Montreal Battery of Evaluation of Amusia (MBEA; Peretz et al., 2003), assessing the presence of amusia, a disorder affecting pitch and melody perception. Participants hear pairs of short melodies and judge whether they are the same or different, across separate pitch and rhythm discrimination tests; (4) the extended Barcelona Music Reward Questionnaire (eBMRQ; Mas-Herrero et al., 2013; Cardona et al., 2022), a 24-item self-report questionnaire that assesses individual differences in sensitivity to music-related reward. The eBMRQ includes subscales for musical seeking, emotion evocation, mood regulation, social reward, sensory-motor, and music absorption. To screen for specific musical anhedonia, only the original BMRQ score (excluding the music absorption items) will be used; and (5) an MRI safety screening questionnaire assessing eligibility criteria for neuroimaging (see Supplementary Materials). If the patient meets all eligibility criteria, they will be enrolled in the study, randomized to either the IML or control group using a computer-generated randomization sequence, and scheduled for a baseline evaluation session. Experimenters will not be blinded to group allocation.

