
A special provision has been established under the DSMP to address potential mental health crises. The Beck Depression Inventory, administered at all in-person evaluations, includes a question assessing suicidal ideation. Responses to this item will be reviewed immediately. If a participant selects a score of 1, 2, or 3, a predefined protocol will be activated. Participants assessed to be at acute risk will be referred for emergency psychiatric care, either through a hospital emergency department or via 911. Those experiencing significant but non-acute distress will be provided with appropriate clinical resources, including a list of wellness tools, self-care apps, and mental health clinics in New York City that accept various insurance plans (see Supplementary Materials).

All data will be keyed with an anonymous code. All personal information will be treated as confidential; only authorized personnel will have access to this data, and it will not be given to third parties without the subject’s explicit consent. All personally identifiable information will be stored in a secure, encrypted server maintained explicitly for the storage of highly sensitive data, including protected health information. Only the research team will have access to this encrypted data. Experimental results, devoid of any personal information that could identify them, will be maintained in the principal investigator’s files, and eventually released as an open-source database. Results will be reported in peer-reviewed journals. Study completion is expected by Fall 2026.

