**Feasibility Measures**							
Burden Ratings (Patients)		X		X		X	X
Acceptability Ratings (Patients)					X		
Feasibility Ratings (Team Member)					X		
Fidelity Ratings (Team Member)					X		

**Table 2. T2:** Outcome measures and benchmarks for success.

Outcome	Description	Benchmark for success
Recruitment	Number of enrolled participants per month	At least 2 per month
Randomization	Proportion of screened patients who are enrolled Proportion of enrolled patients who complete the baseline and pre-intervention evaluations and attend at least one IML/Audiobook session	At least 30% At least 80%
Retention and Adherence	Proportion of enrolled and randomized participants who complete the IML/Audiobook sessions	At least 80% of randomized patients complete at least 80% of the IML/Audiobook sessions
Feasibility	Proportion of listening sessions considered fully feasible; the team member making the phone call will rate the session as “not feasible” , “partially feasible” or “fully feasible”	At least 80% of all sessions considered as fully feasible
Fidelity	Proportion of listening sessions delivered according to the protocol; video calls with patients will be recorded and a team member who was not present during the call will score the session as “delivered according to protocol” or “not delivered according to protocol”	At least 80% of all sessions delivered according to the protocol
Burden	Proportion of planned evaluations that are completed at each time point (baseline, pre-intervention, post-intervention, follow-up) Burden rating: patients will rate each evaluation as “not burdensome” , “partially burdensome” , or “very burdensome”	80% of patients complete the evaluations at each time point At least 80% of patients rate evaluations at each time point as not burdensome
Patient acceptability	Acceptability ratings: patients will rate each listening session as “not acceptable” , “partially acceptable” or “fully acceptable” .	80% of listening sessions rated as fully acceptable

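### Excluding anyone who starts a new treatment is an unlimited post-randomisation exclusion that conflicts with Table 2's randomised denominator for retention and adherence and can bias the results in either direction

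*Protocol article*

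**What the plan says.** The Study population section allows participants to continue existing medications and complementary therapies, but "they will be instructed not to initiate any new medications or therapies during the study period". The next sentence sets the consequence: "Participants who begin a new treatment during the study will be excluded from the analysis". It does not say which analysis, which treatments or which part of the study is meant.

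The Screening section places allocation before baseline: eligible patients are "randomized to either the IML or control group using a computer-generated randomization sequence, and scheduled for a baseline evaluation session". It adds: "Experimenters will not be blinded to group allocation".

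Table 2 describes the primary retention and adherence outcome as a proportion of enrolled and randomised participants. Its benchmark is: "At least 80% of randomized patients complete at least 80% of the IML/Audiobook sessions".

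The Statistical analysis section describes analyses of the feasibility outcomes only: percentages, one-sided tests against the benchmarks, comparison between arms, and factors associated with feasibility. It makes no exception to the exclusion.

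The Ethics and dissemination section contains the safety provision triggered by the suicidal-ideation item of the Beck Depression Inventory. Participants at acute risk are referred for emergency psychiatric care. For people whose distress is marked without being acute, the text says that they "will be provided with appropriate clinical resources, including a list of wellness tools, self-care apps, and mental health clinics in New York City".

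**The concern.** Beginning a treatment happens after randomisation. It may plausibly reflect worsening health, engagement with the study, or the arm itself. Removing people on that basis breaks the comparison that randomisation set up and changes the group to which the feasibility rates apply.

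Four things are at stake:

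- **The primary denominator.** A randomised participant who starts a treatment is counted under Table 2 and not counted under the Study population section.
- **The other primary outcomes.** Feasibility, fidelity and acceptability count sessions, and burden counts patients. They do not state a randomised denominator, so the contradiction is not explicit there, but dropping a participant would also drop that person's sessions and evaluations.
- **The clinical data.** Mental health and cognition are named as the primary clinical outcomes in the Baseline evaluation session section. Starting treatment for mood is plausibly related to those outcomes.
- **The safety provision.** Someone who acts on a referral or resource list by starting a treatment can meet the exclusion. The two sections do not address each other.

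Staff who know the allocation may also be the ones judging what counts as a new treatment.

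**Working it through.** **Inputs from the protocol article.** Planned size: "We aim to enroll 60 participants (30 per group". Accrual: "we aim to enroll at least five participants per month over the course of 12 months". Benchmark: 80% (Table 2). Test: one-sided exact binomial (Statistical analysis). Alpha is not stated; 0.05 is assumed here, with 0.025 shown for comparison. The rate of new treatments and adherence among those who start one are not given, so they are varied below.

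**Reproducing the plan's figure.** 5 per month × 12 months = 60, which agrees with the stated size. There is no power calculation to reproduce.

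**Length of exposure to the rule.** 4 weeks pre-intervention + 4 weeks intervention + 3 months (about 13 weeks) = about 21 weeks from baseline, all after randomisation. The listening sessions occupy only weeks 5 to 8.

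**What the full denominator requires.** 0.80 × 60 = 48 completers for the point estimate. For one-sided exact significance, 54/60 is needed at 0.05 (p = 0.031) and 55/60 at 0.025.

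**Fixed completers s, with k excluded, all assumed non-adherent.** Proportion = s/(60 − k); p = P(X ≥ s) with X ~ Bin(60 − k, 0.80).

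| s | k | Proportion | One-sided exact p |
|---|---|---|---|
| 45 | 0 | 45/60 = 75.0% | 0.87 |
| 45 | 4 | 45/56 = 80.4% | 0.55 |
| 45 | 6 | 45/54 = 83.3% | 0.34 |
| 50 | 0 | 50/60 = 83.3% | 0.32 |
| 50 | 6 | 50/54 = 92.6% | 0.010 |

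With 45 completers the point estimate crosses 80%, but the exact test is nowhere near significance. With 50 completers the test result itself changes.

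**How extreme this assumption is.** If starting a treatment were unrelated to adherence, the chance that all 4 excluded came from the 15 non-adherent is C(15,4)/C(60,4) = 1,365/487,635 = 0.003. The chance that all 6 came from 10 non-adherent is C(10,6)/C(60,6) = 210/50,063,860, about 0.000004. The table therefore shows what a strong association would do, not what to expect.

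**The opposite direction.** 48/60 = 80.0% meets the benchmark. Excluding 6 adherent starters gives 42/54 = 77.8%, which misses it.

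**Expected shift under milder assumptions.** Let p be adherence among all randomised, x the share starting a treatment, and q adherence among starters. The retained set shows (p − xq)/(1 − x). With p = 0.75:

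| x | q = 0.25 | q = 0.50 | q = 0.75 |
|---|---|---|---|
| 5% | 77.6% | 76.3% | 75.0% |
| 10% | 80.6% | 77.8% | 75.0% |
| 20% | 87.5% | 81.3% | 75.0% |

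If starters adhere better, for example q = 0.90 with x = 10%, the result is (0.75 − 0.09)/0.90 = 73.3%, below the true 75%.

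**Chance of observing at least 80% when true adherence is 75%.** All 60 analysed: 0.23. With x = 10% and q = 0.50 (n = 54): 0.32. With x = 20% and q = 0.25 (n = 48): 0.93.

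**The case against.** The exclusion follows directly on text about medications that may affect brain function and about complementary therapies. That suggests a worry about confounded clinical and biomarker data, and Table 2 gives retention and adherence its own denominator. Read as limited to clinical outcomes, the conflict disappears. An article may also leave analysis sets to a fuller document.

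That reading is possible, but the text does not contain it. The only analyses the article describes are of feasibility. Limiting the rule to clinical outcomes would still leave a post-randomisation exclusion there. The article also did not leave the matter open: it states a rule, and an analysis plan that followed it would inherit the conflict.

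Other parts of the objection stand and limit the point. A reader might infer that:

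- **The rule removes everyone the safety provision refers.** It does not. A referral or a resource list is not itself a new treatment; only those who then start one can be removed.
- **The exclusion is outcome-related and makes feasibility look better.** The documents do not establish this. The rule covers any medication or therapy, and the working shows no expected shift, or a fall, under other assumptions. About three of the five months fall after the sessions end, when a new treatment cannot affect adherence, although exclusion would still delete adherence already recorded.
- **All primary outcomes have contradictory denominators.** Among the primary outcomes, only retention and adherence is explicitly set on randomised patients.

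The Discussion also says that the trial is not powered for clinical change, so the harm to the clinical data concerns their value for later planning, not a test in this trial.

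**Conclusion.** The concern holds in this limited form. As written, the exclusion is unqualified, acts entirely after randomisation in an unblinded study, and cannot be reconciled with the retention and adherence row of Table 2. That contradiction needs no assumption about who starts a treatment.

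The size and direction of any bias do depend on assumptions. Four exclusions out of 60 can move a missed benchmark to a met one as a point estimate, and six can change the exact test from p = 0.32 to p = 0.010, but only if everyone excluded was non-adherent. With no association between starting treatment and adherence the expected shift is nil, and with better adherence among starters the rate falls. The frequency of new treatments is unknown.

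Because a primary benchmark can turn on so few people, and the rule is easily replaced, it should be corrected before analysis. The exclusion and the safety provision must also be reconciled; this review takes no position on clinical management.

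**What to change.** Replace the exclusion sentence with a statement that all randomised participants are analysed in their allocated arm for every feasibility and clinical outcome. Record new treatments as post-randomisation events and report type and start date by arm. Confine any exclusion, or any setting aside of data after a new treatment began, to a labelled sensitivity analysis of the clinical outcomes. State how a treatment begun after a safety referral is handled in the analysis, so that the Study population and Ethics and dissemination sections agree.

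The cost is small and no extra participants are needed. The text change is a few sentences. Medications and complementary activities are shown as collected at baseline only (Baseline evaluation session section, Table 1), so a brief update at the pre-intervention, post-intervention and follow-up visits would have to be added.

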### Procedures and assessments

#### Screening

Eligibility will be assessed using a well-characterized stroke registry. Initial screening will verify age and confirm a diagnosis of ischemic or hemorrhagic stroke occurring at least six months prior to enrollment. Additional exclusion criteria will then be reviewed. If data for key screening measures are missing from the registry, a study team member will contact the patient to explain the study and gauge interest. If the patient agrees to participate, they will complete a screening session (online or in person) to confirm eligibility. This session may include: (1) the Hearing Handicap Inventory for the Elderly – Screening version (HHIE-S; Ventry & Weinstein, 1982), a 10-item self-report measure of hearing loss validated against pure-tone audiometry (Lichtenstein et al., 1988); (2) the Montreal Cognitive Assessment (MoCA), a standardized screening tool used to detect cognitive impairment and early signs of dementia (Nasreddine et al., 2005). The MoCA assesses multiple cognitive domains, including executive function (e.g., trail-making), visuospatial abilities (e.g., clock-drawing), attention (e.g., digit span), language (e.g., sentence repetition and verbal fluency), abstraction (e.g., identifying similarities between two concepts), short-term memory (via a delayed recall task), and orientation (e.g., stating the current date, month, and year); (3) the Montreal Battery of Evaluation of Amusia (MBEA; Peretz et al., 2003), assessing the presence of amusia, a disorder affecting pitch and melody perception. Participants hear pairs of short melodies and judge whether they are the same or different, across separate pitch and rhythm discrimination tests; (4) the extended Barcelona Music Reward Questionnaire (eBMRQ; Mas-Herrero et al., 2013; Cardona et al., 2022), a 24-item self-report questionnaire that assesses individual differences in sensitivity to music-related reward. The eBMRQ includes subscales for musical seeking, emotion evocation, mood regulation, social reward, sensory-motor, and music absorption. To screen for specific musical anhedonia, only the original BMRQ score (excluding the music absorption items) will be used; and (5) an MRI safety screening questionnaire assessing eligibility criteria for neuroimaging (see Supplementary Materials). If the patient meets all eligibility criteria, they will be enrolled in the study, randomized to either the IML or control group using a computer-generated randomization sequence, and scheduled for a baseline evaluation session. Experimenters will not be blinded to group allocation.

#### Baseline evaluation session

During the baseline evaluation session, we will first collect measures of *individual differences*, including (1) demographics: age, gender, race, ethnicity, dominant hand, languages spoken, current medications (with dosages), participation in complementary health activities (e.g., yoga, meditation), occupational status, and highest education level (see Supplementary Materials); (2) music/audiobook preferences: participants will report their preferred genres (e.g., music: classical, pop, jazz; audiobooks: science fiction, noir, biography), favorite artists/authors, and mood-based music/audiobook preferences to support individualized playlist creation (see Supplementary Materials). Both groups will also provide a list of songs that elicit chills or intense emotional responses, which will be used as stimuli during fMRI scanning; and (3) the Goldsmiths Musical Sophistication Index (Gold-MSI): a 38-item self-report questionnaire assessing musical expertise across dimensions such as active engagement, perceptual ability, training, singing skill, and emotional responsiveness (Müllensiefen et al., 2014). Next, participants will complete behavioral questionnaires assessing *mental health* and *cognitive functioning*, which serve as the primary clinical outcomes. While the main focus is on the impact of IML on mental health, cognitive measures are included to capture domains previously shown to improve with music listening interventions (Särkämö et al., 2008; Sihvonen et al., 2020).

The *mental health measures* will include: (1) the Beck Depression Inventory (BDI), a 21-item self-report questionnaire designed to assess the severity of a person’s depression symptoms (Beck et al., 1961); (2) the Stroke-Specific Quality of Life (SS-QOL), a 49-item self-report questionnaire designed to assess the health-related quality of life specific to survivors of stroke (Williams et al., 1999). It contains 12 subscales: energy, upper extremity function, work, mood, self-care, social roles, family roles, vision, language, thinking, and personality; (3) the Perceived Stress Scale (PSS), a 10-item questionnaire that assesses the degree to which individuals perceive situations in their lives as stressful (Cohen et al., 1983); (4) the Generalized Anxiety Disorder-7 (GAD-7), a 7-item self-report questionnaire that assesses the severity of generalized anxiety symptoms (Spitzer et al., 2006); (5) the Positive and Negative Affect Schedule (PANAS), a 20-item self-report questionnaire designed to assess positive and negative affect (Watson et al., 1988). The scale consists of two 10-item subscales, each measuring the extent to which individuals have experienced a range of positive (e.g., enthusiastic, inspired) or negative (e.g., upset, nervous) emotions; and (6) the World Health Organization Well-Being Index (WHO-5), a 5-item questionnaire designed to assess the mental well-being of individuals, including aspects of vitality, emotional state, and life satisfaction (Topp et al., 2015).

The *cognitive functioning* measures will be assessed using the NIH Toolbox Cognition Battery (Weintraub et al., 2013). We will assess cognitive functioning across several domains: (1) processing speed, using the Oral Symbol Digit Test, a timed task in which participants match symbols to numbers; (2) working memory, using the List Sorting Working Memory Test, which requires participants to recall and sequence items presented both visually and aurally; (3) verbal memory, using the Rey Auditory Verbal Learning Test, where participants are asked to freely recall as many words as possible from a list of 15 unrelated words; and (4) attention, using the Flanker Inhibitory Control and Attention Task, which evaluates the ability to focus on a central stimulus while inhibiting attention to surrounding distractors.

At the end of the evaluation session, participants will also complete a *burden rating*, indicating whether they found the session “not burdensome,” “partially burdensome,” or “very burdensome.”

